#### 6.5.4 Treatment of nausea/ vomiting

For acute nausea and vomiting, a 5-HT3 antagonist with corticosteroids prior to infusion would be considered standard premedication. For delayed nausea and vomiting, an oral 5-HT3 antagonist is the first option; metoclopramide, alizapride and prochlorperazine may be also used.

#### 6.5.5 Treatment of diarrhea

Symptoms of diarrhea and/or abdominal cramping may occur at any time and should be managed according to standard institutional practice.

Subjects should also be instructed to notify the investigator or nurse for the occurrence of bloody or black stools, symptoms of dehydration, fever, inability to take liquids by mouth, inability to control diarrhea (return to baseline) within 24 hours. Subjects with diarrhea should be evaluated frequently by a nurse or physician until resolution of diarrhea.

Changes in electrolytes, even without BUN/urea and/or creatinine elevation, may reflect early physiologic consequences of treatment-induced gastrointestinal toxicity. Subjects with clinically significant electrolyte changes should be evaluated for dehydration and receive aggressive fluid and electrolyte replacement, if indicated.

A prophylactic treatment is not recommended. As soon as signs of diarrhea occur, the patient should immediately consult his physician and start with the intake of loperamide: 2 capsules (4 mg), thereafter 1 capsule (2 mg) every two hours, for at least 12 hours and for at least 12 hours after the last observation of liquid stool. The use of drugs with laxative properties should be avoided because of the potential for exacerbation of diarrhea. Patients should be advised to contact their physician to discuss any laxative use. Sufficient oral rehydration has to be administered during the whole diarrhea episode.

If diarrhea is severe (requiring intravenous rehydration) and/or associated with fever or severe neutropenia (Grade 3 or 4), broad-spectrum antibiotics must be prescribed. Patients with severe diarrhea or any diarrhea associated with severe nausea or vomiting **must be hospitalized** for intravenous hydration and correction of electrolyte imbalances. In case of persisting severe diarrhea despite loperamide treatment, this drug should be replaced by another antidiarrheal therapy (e.g. octreotide).

#### 6.5.6 Electrolyte management

Subjects should be evaluated as outlined in section 5 and managed as per local medical practice. If hypomagnesemia is present, replacement should be managed with either oral or parental replacement, or both, according to institutional practice and to the degree of hypomagnesemia present. It is recommended that subject's serum magnesium level should be maintained within the normal range during study treatment.

It is important to assess and manage serum potassium and calcium (adjusted for albumin) in subjects who have concomitant hypomagnesemia. Subject's serum potassium and calcium parameters are recommended to be maintained, as per local medical practice, within the normal ranges during study treatment.

#### **6.5.7 Prevention and treatment of neutropenia**

Hematopoietic growth factors (i.e., filgrastim or pegfilgrastim) may be used according to institutional or other specific guidelines (e.g. ASCO, EORTC) to treat febrile neutropenia. Due to the high risk of neutropenia together with gastrointestinal toxicity, secondary prophylactic use of G-CSF should be considered after the first chemotherapy associated episode of neutropenia > grade 2, especially in patients >60 years.

Use of any supplementary growth factor must be documented in the patient record. Growth factors must be discontinued at least 48 hours prior to initiation of the next cycle of chemotherapy.

Prophylactic treatment with antibiotics is not allowed.

#### **6.5.8 Prohibited Medications**

Patients should not receive any of the following medications during the treatment period:

- any other antineoplastic treatment
- any other medication for skin toxicity *prophylaxis*
- antibiotics for prophylaxis of hematological toxicity
- other investigational therapies

## 7 Assessment of Safety

The Investigator's Brochure will be used as reference document for panitumumab and will be provided to the investigators in the investigator's file.

### 7.1 Definitions of Adverse Events and Serious Adverse Events

#### 7.1.1 Adverse Event

An adverse event is defined in the International Conference on Harmonization (ICH) Guideline for Good Clinical Practice as "any untoward medical occurrence in a patient or clinical investigation subject administered a pharmaceutical product and that does not necessarily have a causal relationship with this treatment" (ICH E6:1.2).

An adverse event can therefore be any unfavorable and unintended sign (including an abnormal laboratory finding, for example), symptom or disease temporally associated with the use of a medicinal product, whether or not it is considered related to the medicinal product.

#### 7.1.2 Adverse Drug Reaction

All untoward and unintended responses to a medicinal product related to any dose administered.

The phrase "responses to a medicinal product" means that a causal relationship between the medicinal product and the adverse event is at least a reasonable possibility, i.e., the relationship cannot be ruled out.

A serious ADR (SADR) is an ADR that meets the definition of serious (provided below).

#### 7.1.3 Serious Adverse Event

A serious adverse event (SAE) is defined as an adverse event that

- is fatal
- is life threatening (places the subject at immediate risk of death)
- requires in-patient hospitalization or prolongation of existing hospitalization
- results in persistent or significant disability/incapacity
- is a congenital anomaly/birth defect
- other significant medical hazard

For this study, the following is **not** classified as serious adverse event:

- Progression or deterioration of the malignancy under study (including new metastatic lesions) or death due to progression unless the investigator deems it to be related to the use of study treatments.

- Hospitalizations for the performance of protocol-required procedures or administration of study treatment
- Hospitalizations or procedures planned prior to study start or elective hospitalizations

A hospitalization meeting the regulatory definition for “serious” is any inpatient hospital admission that includes a minimum of an overnight stay in a healthcare facility. Any adverse event that does not meet one of the definitions of serious (e.g., visit to A&E, outpatient surgery, or requires urgent investigation) may be considered by the investigator to meet the “other significant medical hazard” criterion for classification as a serious adverse event. Examples include allergic bronchospasm, convulsions, and blood dyscrasias.

#### 7.1.4 SUSAR

A SUSAR is defined as a suspected unexpected serious adverse reaction. An unexpected adverse event is any adverse drug event, the specificity or severity of which is not consistent with the current investigator’s brochure for panitumumab. Also, reports that provide significant information on the specificity or severity of a known, already documented adverse event constitute unexpected adverse events. An event more specific or more severe than described in the investigator’s brochure would be considered “unexpected”. All suspected adverse reactions related to panitumumab which occur in the trial and that are both unexpected and serious (SUSARs) are subject to expedited reporting.

## 7.2 Reporting of SAEs

Any clinical adverse event or abnormal laboratory test value that is serious occurring during the course of the study from the date of signing the informed consent, irrespective of the treatment received by the patient, must be reported to the sponsor within 24h of knowledge (expedited reporting) per European Union Guidance CT3 (R2). For each patient, all serious adverse events should be reported up to 30 days after the last dose of investigational product. Serious adverse events with relation to the IMP occurring more than 30 days after a patient is discontinued from the study treatment must be reported to the Sponsor.

The completed SAE form must be faxed to:

**ClinAssess GmbH**  
**[name], [name]**  
**[contact]**

The sponsor will medically review all SAEs.

It is possible that Amgen may request follow-up information via the sponsor.

The following detailed information must be recorded for each serious adverse event in the SAE report form:

- A description of the AE in medical terms preferably according to NCI-CTCAE Version 4.03, not as reported by the subject
- The severity grade as assessed by the investigator according to the definitions in NCI-CTCAE Version 4.03
- The date of becoming serious and the date of becoming known (if different)
- The reason for seriousness
- The outcome of the SAE at the time of the report
- Information on administration of the study drug and chemotherapy and any action taken
- Information on any treatment procedures necessary for the SAE, concomitant medications, relevant lab tests and relevant medical history

If in any one subject the same SAE occurs on several occasions, then the SAE in question must be documented and assessed anew each time.

The investigator is required to submit SAE Follow-up reports until the SAE has resolved or stabilized and all queries have been answered.

### **7.3 Reporting of SUSARs**

The sponsor will ensure the notification of the appropriate ethics committees, competent authorities and participating investigators of all SUSARs events occurring at the sites in accordance with local legal requirements, statutes and the European Clinical Trial Directive as follows:

- Reporting of the SUSAR to the Competent Authorities and Ethics Committees within 15 days (or within 7 days for fatal and life-threatening events)
- Sending the event to all participating Investigators for information (with confirmation of receipt).

In addition, all events that require a new assessment of the risk-benefit ratio will be reported to the Ethics Committee and the Competent Authority of each concerned Member State within 15 days. This includes:

- Single reports of expected serious adverse reactions with unexpected outcome.
- An increase in the rate of occurrence of expected serious adverse reactions which is judged to be clinically relevant
- Post-study SUSARs that occur after the patient has completed a clinical trial

- New events related to the conduct of the trial or the development of the investigational medicinal products and likely to affect the safety of the subjects

The sponsor is responsible to ensure that the latest investigator's brochure is used as the source document for determining the expectedness of an SAE.

#### 7.4 Recording of Adverse Events

The investigator is responsible for ensuring that all adverse events observed by the investigator or reported by subjects are properly recorded in the subjects' medical records and the case report form.

The following adverse event attributes must be assigned by the investigator:

- Adverse event term according to the NCI-CTCAE criteria Version 4.03
- Severity grade according to the NCI-CTCAE criteria Version 4.03
- Start date and stop date (or date of last assessment)
- Outcome
- Causality to study drug and chemotherapy (to be assessed as either related or unrelated)
- Any action taken

Adverse events will be followed until they resolve to baseline or considered stable. It will be left to the investigator's clinical judgment to determine whether an adverse event is related and of sufficient severity to require the subject's removal from treatment or from the study. A subject may also voluntarily withdraw from treatment due to what he or she perceives as an intolerable adverse event. If either of these situations arises, the subject should be strongly encouraged to undergo an end-of-study assessment and be under medical supervision until symptoms cease or the condition becomes stable.

Pre-existing diseases, when worsening during study therapy, have to be considered as adverse events. They can lead to serious adverse events, if they meet the criteria described in section 7.1.3.

Intensity of adverse events will be graded using the National Cancer Institute Common Terminology Criteria for Adverse Events (CTCAE), version 4.03 (see investigator's file). If an adverse event occurs which is not described in the CTCAE version 4.03, the four-point scale below will be used.

|           |                                                               |
|-----------|---------------------------------------------------------------|
| Mild:     | Discomfort noticed but no disruption of normal daily activity |
| Moderate: | Discomfort sufficient to reduce or affect daily activity      |
| Severe:   | Inability to work or perform normal daily activity            |

Life-threatening: Represents an immediate threat to life

## 7.5 Laboratory Test Abnormalities

Laboratory test results will be recorded on the laboratory results pages of the case report form. In the event of unexplained abnormal laboratory test values, the tests should be repeated immediately and followed up until they have returned to the normal range and/or an adequate explanation of the abnormality is found.

Laboratory test value abnormalities as such should not be reported on the AE page of the CRF as adverse events unless they are treatment-emergent and they satisfy one or more of the following conditions for clinical significance:

1. Accompanied by clinical symptoms
2. Leading to a change in study medication (e.g., dose modification, interruption or permanent discontinuation)
3. Requiring a change in concomitant therapy (e.g., addition of, interruption of, discontinuation of, or any other change in a concomitant medication, therapy or treatment)

Please note: Any laboratory result abnormality fulfilling the criteria for a serious adverse event (SAE) should be reported as such, in addition to being recorded as an adverse event in the CRF.

## 7.6 Pregnancy

Female patients must be instructed to immediately inform the investigator if they become pregnant during the study. The study treatment must immediately be stopped. Pregnancies occurring up to 6 months after the completion of the last treatment cycle must also be reported to the investigator. The investigator must report all pregnancies within 24 h to ClinAssess. ClinAssess will forward all pregnancy reports to the sponsor within one working day. The investigator should counsel the patient; discuss the risks of continuing the pregnancy and the possible effects on the fetus. The patient should be monitored until the conclusion of the pregnancy. Follow up case reports have to be provided as new information becomes available.

Pregnancy occurring in the partner of a patient participating in the study should also be reported to the investigator, the sponsor and the CRO. The partner should be counseled and followed as described above.

### **7.7 Adverse Drug Reactions with Concomitant Medication**

The investigators must be aware that for all concomitant medications the regulations of post-marketing reporting for suspected adverse drug reactions apply, i.e., reporting to the marketing authorization holder or the local regulatory bodies.

## 8 Biostatistical Aspects

### 8.1 Trial Design and Hypotheses

This trial is designed as a randomized, parallel-group, open label, multicentre, phase II trial with formal “within-trial” comparison in order to show any beneficial effect of maintenance plus panitumumab compared to maintenance alone in terms of progression-free survival. The following hypothesis system will be subjected to statistical analysis:

Null Hypothesis  $H_0$ :  $HR = 1$  vs. Alternative Hypothesis  $H_1$ :  $HR < 1$ ,

where HR denotes the ratio of the hazard of progression/death with arm A divided by the hazard of progressions/death with arm B.

### 8.2 Sample Size Calculation

The sample size required within this trial is calculated based on the hypothesis system described in section 8.1. To estimate the number of events (progressions or deaths, whichever first) required within the Full Analysis Population in this study, the following assumptions are made:

- One-sided Log-rank test will be applied for comparison of PFS between treatment arms.
- The one-sided significance level is set to 10%. This reflects the goal of the phase II to
  - allow for unbiased evaluation of any potential superiority of 5-FU/FA plus panitumumab compared to 5-FU/FA alone
  - generate sufficient data for preliminary assessment of the clinical relevance of the maintenance treatment with 5-FU/FA plus panitumumab
  - provide a sensible gate-keeper for further development and
  - support further decision making within the community and
  - last but not least decide whether a Phase III trial is justified.
- Progression-free survival follows an exponential distribution.
- Median PFS in patients treated with maintenance lacking panitumumab is expected to be roughly 7.5 months. This is derived by considering OPTIMOX2 showing a median PFS of 8.6 months in patients treated with mFOLFOX7 during induction followed by simplified LV5FU2 therapy thereafter. Excluding the first 3 months of induction therapy and excluding progressions and other cases where patients are not eligible for randomization after 3 months which do not start maintenance therapy, will lead to a median progression-free survival (calculated from date of randomisation) of roughly 7.5 months.

- On the other hand, previous phase III studies (e.g., PRIME-study) have shown that adding panitumumab can lead to prolongation of PFS with hazard ratios (HR) ranging between 0.7 and 0.8. Based on this data, 5-FU/FA+panitumumab will be considered to be clinically relevant if it is associated with a HR of 0.75; this converts into a median PFS of 10 months.
- The power to yield statistical significance if the HR is in fact 0.75 is set to 80%.
- All patients are to be followed until progression or death whatever occurs first. 5% of patients will be assumed to be continuously lost during the study period per year.

Based on the assumptions above, a logrank test for comparing the progression-free survival curves will have 80% power to reject the null-hypothesis if the true hazard ratio is 0.75 with a total number of 218 events (progressions or deaths, whichever occurs first).

Since the power of any time-to-event study is determined by the number of events rather than the number of patients, there is a range of sample sizes that meet the objectives of this trial. Naturally, the more patients being followed, the sooner the desired number of events will be observed. Assuming that with roughly 9 patients starting the induction phase, 8 patients per month can actually be randomized thereafter, the required number of events will be expected to occur within a total study duration (including follow-up) of roughly 108 months with at most 252 patients qualifying for Full Analysis population. To account for the fact that merely roughly 90% of patients treated with mFOLFOX6+panitumumab will show CR, PR or SD, but a relevant drop-out for various reasons (including patients with secondary resections who were therefore not eligible for randomisation) occurs after induction therapy, a total of approx. 400 patients should be enrolled to the trial to ensure that 252 patients enter the randomisation and receive maintenance treatment.

If a more rigid significance level of one-sided 5% is required, the above mentioned sample size allows demonstrating statistical significance with a power of roughly 69%. However, if the true HR is 0.714 or less (i.e., if the median PFS associated with 5-FU/FA+panitumumab is at least 10.5 months), statistical significance at the 5% significance level can be ensured with a power of 80%.

## 8.3 Evaluation Categories for Patients

### 8.3.1 Full Analysis Population

The Full Analysis Population is used to perform the Intent-to-Treat (ITT) analysis and includes all randomized patients who received at least one dose of maintenance treatment (irrespective of substance) according to the study protocol. Patients within the ITT will be analyzed in their initial group of randomization.

Furthermore, the Full Analysis Population for the whole study, the induction phase and the maintenance phase will be defined, including all patients who received at least one dose of study treatment in the respective study phase.

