| Planned sample size    | Approx. 400 patients will be enrolled to reach the planned number of 272 randomizations                                                                                                                                                                                                                                                                                                                                                                                                                                                                                                                                                                                                                                                                                                                                                                                                                                                                                                                                                                                                                                                                                                                                                                                                                                                                                                                                                                                                                                                                                                                                                                                                                                                                                                                                                                                                                                                                                                    |

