### 3 Investigational Plan

#### 3.1 Overview of Study Design and Dosing Regimen

This is a phase II, randomized, multi-center, open-label, parallel-group study to evaluate the progression-free survival during maintenance therapy.

Eligible patients will be treated within a 12-week induction therapy. Those patients achieving CR/PR or SD at 12 weeks and qualifying for maintenance treatment and re-induction treatment with all potential drug components, will be randomized in a ratio of 1:1 to receive chemotherapy plus panitumumab (arm A) or chemotherapy alone (arm B) during maintenance. In case of progression, re-induction treatment will be started.

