Time-to-event data will be analyzed by Kaplan-Meier methods, when merely non-informative censoring occurs. For statistical comparison, the logrank-test will be provided supplemented by multivariate Cox proportional hazards models.

The primary endpoint of this trial will be subjected to confirmatory statistical hypothesis testing applying the one-sided significance level of 10%. All other statistical tests are to be interpreted on an exploratory perspective. Consequently, no adjustment for multiple testing is foreseen.

Confirmatory statistical analysis of the primary efficacy parameter will be performed within the Full Analysis Population (Intent-to-Treat analysis). The Per Protocol Population merely serves for sensitivity analysis. All safety analyses will be performed within the Safety Population.

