### **8.5 Interim and Final Analysis**

No confirmatory interim analyses for efficacy with the aim to stop the trial prematurely due to proof of efficacy or futility are foreseen within the study protocol.

The primary confirmatory statistical analysis of this trial is performed whenever at least 218 events (first progressions/deaths) are documented within the Full Analysis population. The final analysis will be performed with a minimum follow-up of 2 years after randomization of the last subject available for each patient randomized to the trial.

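### The primary analysis set is labelled intention-to-treat but leaves out randomised patients who start no maintenance, and no PFS analysis of all randomised patients is specified

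*Protocol*

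**What the plan says.** Section 8.3.1 says that the Full Analysis Population serves the intention-to-treat analysis and that it "includes all randomized patients who received at least one dose of maintenance treatment (irrespective of substance) according to the study protocol". Members are analysed in the arm to which they were randomised.

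Section 8.4.1 places the confirmatory test there: "Confirmatory statistical analysis of the primary efficacy parameter will be performed within the Full Analysis Population (Intent-to-Treat analysis"). On the alternative set it says: "The Per Protocol Population merely serves for sensitivity analysis". Section 8.3.2 builds that Per Protocol set by removing further patients from the Full Analysis Population.

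Section 8.5 ties the timing to the same set: the primary analysis is "performed whenever at least 218 events (first progressions/deaths) are documented within the Full Analysis population".

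Section 8.4.3 starts the PFS clock at the date of randomisation. Section 3.1 gives the design: "This is a phase II, randomized, multi-center, open-label, parallel-group study to evaluate the progression-free survival during maintenance therapy".

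On numbers, the Synopsis says "Approx. 400 patients will be enrolled to reach the planned number of 272 randomizations", and sections 3.2 and 3.3 repeat 272. Section 8.2 plans for no more than 252 patients in the Full Analysis Population and sizes enrolment "to ensure that 252 patients enter the randomisation and receive maintenance treatment".

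**The concern.** An intention-to-treat comparison keeps everyone who was randomised, so that the arms differ only by chance and by assigned treatment. Here, membership of the primary set is decided by something that happens after randomisation, in a trial where patient and investigator can know the arm before the first maintenance dose. A randomised patient who progresses or dies before that dose has a PFS event under section 8.4.3, yet that event enters neither the test nor the count of 218.

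If failing to start maintenance is more common in one arm and is also related to prognosis, the arms in the analysis are no longer comparable and the one-sided 10% level no longer holds. Section 8.2 gives unbiased evaluation and the decision on a phase III trial as goals, so this matters for the only confirmatory endpoint. Nothing planned would show the effect, because every PFS comparison between the arms is made in the dosed set or a subset of it.

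**Working it through.** **1. Reproduce the event number.** Inputs from section 8.2: HR 0.75, one-sided alpha 10%, power 80%; 1:1 allocation from section 3.1. Schoenfeld formula:

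d = 4 × (z₀.₉₀ + z₀.₈₀)² / (ln 0.75)² = 4 × (1.2816 + 0.8416)² / (0.2877)² = 217.9, rounded up to 218.

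This matches the protocol. The formula does not depend on which population carries the events, so 218 is not in dispute.

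**2. Compare the two patient numbers.** 272 − 252 = 20, and 20/272 = 7.4%. The event fraction would be 218/252 = 86.5% in the dosed set and 218/272 = 80.1% in all randomised patients. Section 8.2 does not explain the gap. The attrition it describes (no CR, PR or SD; secondary resection) comes before randomisation, and it uses 252 as the number who enter randomisation.

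**3. Effect on the error rate.** The documents give no rate, arm split or prognosis for non-starters, so this is a range under assumptions. Simulation: 272 randomised 1:1, uniform entry over 84 months, exponential PFS with median 7.5 months, 5% yearly loss, cut at 218 events in the set tested, unstratified log-rank test at one-sided 10%, no treatment effect, 4,000 runs per scenario. Each arm has 20 patients whose median PFS takes the value shown; 20 of these 40 never start and are dropped from the dosed set.

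| Median PFS of that group | Dropped A / B | Rejection, dosed set | Rejection, all randomised |
|---|---|---|---|
| 3 months | 10 / 10 | 9.5% | 9.7% |
| 3 months | 15 / 5 | 18.5% | 9.3% |
| 3 months | 20 / 0 | 29.3% | 10.1% |
| 3 months | 5 / 15 | 5.0% | 10.0% |
| 3 months | 0 / 20 | 2.0% | 9.4% |
| 5 months | 15 / 5 | 14.1% | 10.2% |
| 5 months | 5 / 15 | 7.3% | 10.0% |
| 7.5 months (as the rest) | 15 / 5 | 9.9% | 9.7% |
| 7.5 months (as the rest) | 5 / 15 | 10.2% | 10.1% |
| 15 months | 15 / 5 | 4.0% | 9.2% |
| 15 months | 5 / 15 | 18.6% | 9.2% |

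The Monte Carlo standard error near 10% is √(0.1 × 0.9 / 4000) = 0.5 points. A balanced split, or non-starters with average prognosis, leaves the dosed set near 10%. Only the combination of arm imbalance and prognostic difference moves it, and it moves in either direction. The all-randomised test stays near 10% throughout.

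Milder departures matter less. In a second simulation of the same design (6,000 runs per scenario, three-fold hazard, i.e. median 7.5/3 = 2.5 months), splits of 12/8, 6/2 and 3/1 gave 13%, 12% and 11%, and 8/12 gave 7%.

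**4. Effect on power.** Same set-up with HR 0.75 and 10 non-starters per arm who gain nothing from panitumumab: power is 79.0% in the dosed set and 75.0% in all randomised patients. The 218th event falls at a median of 89.4 and 82.6 months respectively, about 7 months earlier in all randomised patients.

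**The case against.** The best defence is that a dosed-only set analysed as randomised is a familiar modified intention-to-treat set, and that non-starting should be rare: only patients with disease control who qualify for all maintenance and re-induction drugs are randomised. Both may be true. The first argues for naming the set correctly. The second is an expectation that the protocol does not quantify.

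Several stronger readings are tempting, and the text does not support them.

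- A reader might infer that 272 against 252 is a planned loss of 20 non-starters, or 7.4%. No section says so, and section 8.2 treats 252 as a randomisation figure. The two numbers are an unexplained mismatch to be reconciled.
- A reader might infer that an arm A patient who refuses further panitumumab because of skin toxicity is dropped. Both arms receive 5-FU/FA and the definition counts a dose of any substance, so that patient stays in arm A. Only patients who take no maintenance at all are removed.
- A reader might take the closing words of the definition, on accordance with the protocol, as a further filter. Section 8.3.2 removes patients given the wrong treatment from the Full Analysis Population to form the Per Protocol set, which suggests that they belong to the former. The wording is ambiguous, no more.

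The protocol also contains part of the remedy. Section 8.2 assumes that all patients are followed to progression or death. Section 5.4 keeps patients who withdraw consent only for treatment under follow-up for progression and survival. Section 8.4.3 counts all deaths after randomisation for overall survival, although that analysis follows the primary one by analogy and does not clearly name an all-randomised set. Section 8.3.1 mentions a whole-study Full Analysis Population, which would include randomised patients dosed only in induction, but no PFS comparison by arm is assigned to it.

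**Conclusion.** The point holds as a defect in the definition. The confirmatory test and its event trigger sit in a modified intention-to-treat set under an intention-to-treat label, membership is settled after an open-label assignment, and no all-randomised PFS analysis backs it up.

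The size and sign of any bias are unknown. The range of about 5% to 18-19% rests on assumptions that the documents do not supply: 20 non-starters, a median PFS of 3 months for them, and a three-to-one arm split. More extreme assumptions widen it, and balanced or uninformative non-starting removes it. A reader might infer that the randomised comparison is already broken or that false positives are inflated. The documents show only that the plan does not guarantee the 10% level. The event number of 218 stands.

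**What to change.** In section 8.3.1, define the primary set as all randomised patients, analysed in their assigned arm, whether or not a maintenance dose was given. Carry this into section 8.4.1, and in section 8.5 count the 218 events in that set. Keep the dosed subset as a sensitivity analysis under the name modified intention-to-treat, and report non-starters by arm with reasons. Reconcile 272 (Synopsis, sections 3.2 and 3.3) with 252 (section 8.2).

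State that randomised but undosed patients stay on the planned 8-weekly tumour assessments. The present rule in sections 5.1.1 and 5.2.4 names patients who discontinue maintenance or re-induction and does not clearly cover those who never began.

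The cost is wording, continued scans for any non-starters, and some power. The target of 218 and the enrolment plan need not change. If about 20 non-starters gain no benefit, power at HR 0.75 is about 75% instead of about 79%, and section 8.2 should say so; recovering the difference would take more events. In the same scenario the 218 events arrive about 7 months sooner.
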